### Assessing the predictive validity of the FI and CI

FI and CI computed at baseline will be used as predictors of health outcomes documented with the LHC at follow-ups. Survival models, adapted to single (e.g., death, diagnosis) or multiple failure (e.g., hospitalizations, falls) sequences [50] will be used. Data will be aligned on first assessment (time-to-event procedure). These analyses will determine the probability of adverse events over time as a function of the FI, respectively CI, initial scores.

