### Objectives

The main purpose of the fraXity study is to develop frailty and complexity index computation algorithms based on the Canadian French version of the interRAI-HC [38]. The frailty index (FI) derivation relies on the available methodology [39]. This well-documented rationale [26–32], further supported by the operational definition proposed in the COMID [37], is used to derive the complexity index (CI). By relying on a prospective observational case-control longitudinal design, the study aims to assess the predictive validity of the proposed indices with respect to undesirable health outcomes (falls, emergency admissions, deaths) and health resource consumption (length of hospital stays, number of physician visits), monitored throughout the course of the study. Three measurement occasions will be used to estimate intra-individual change in frailty and complexity, as assessed with the proposed indices. Finally, by considering different subgroups of the aged population (see below), the study should provide estimates of frailty and complexity rates in a panel of the older population wider than the usual clinical population that interRAI instruments target. Overall, the fraXity study addresses four research questions. (1) Can frailty, respectively complexity, indices be derived from information collected during a comprehensive geriatric assessment done with the RAI-HC? (2) What is the predictive validity of frailty, respectively complexity, indices with respect to adverse health outcomes and health resource consumption? (3) What are the rates of frailty, respectively complexity, in various subsamples of the older population, and how do these rates change over time? (4) Which recommendations for best practices can be drawn from the findings to mount care strategies aimed at reducing the risks of adverse health outcomes related to frailty, respectively complexity?

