### Data sources and measurement

Nurses previously trained to complete comprehensive geriatric assessments with the interRAI-HC and additional instruments will collect the data. On each measurement occasion, participants will receive the interRAI-HC, which provides the outcomes used to derive the frailty (FI) and complexity (CI) indices, and a life history calendar (LHC), which provides the outcomes used to assess the predictive validity of FI and CI.

The interRAI-HC, Canadian French version 9.1 (243 items, 90 min [38]) is a standardized comprehensive geriatric assessment that belongs to a suite of instruments designed for standardized assessment across settings [41] and for consistent information sharing [42]. Version 9.1 of the Canadian French interRAI-HC entails a minimal dataset (MDS) covering the following domains: administrative information (A) and living conditions (B), cognition (C), sensory abilities (D), health-related behavior (E) and social behavior (F), activities of daily living (ADL, G), continence (H), medical diagnoses (I), falls, physical abilities, physical symptoms and pain (J), nutrition (K), skin and feet problems (L), medication (M), ongoing therapies and formal care (N), advanced care instructions and legal representativity (O), informal care (P), living environment (Q), observed change in ADL (R) and record information (S). As previously demonstrated [28–32], the quality and nature of the information collected with the interRAI-HC will be rich enough to derive a variety of additional clinical scores and indices.

The life history calendar (LHC, 15 min [43]). The LHC is a retrospective method used to gather reasonably valid information on past events. The LHC allows for the fine-grained time-to-event recoding of events, and it appears to be well suited to documenting adverse outcomes. As designed for the fraXity study, the tool covers the 6 months preceding each interview. It will assess the history of falls, emergency admissions, hospitalizations and lengths of stays, physician visits and life-striking events (e.g. separation, relocation, death of kin, medical diagnosis).

Additional sociodemographic and health questionnaires will be used to document population characteristics; the choice of the instruments will follow the recommendations of the International Consortium for Health Outcomes Measurement (ICHOM) [44, 45].

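### The predictive-validity models leave out the six-month event history recorded at baseline, so they cannot show that FI or CI add to it

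*Protocol article*

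**What the plan says.** Research question 2 (Objectives) reads: "What is the predictive validity of frailty, respectively complexity, indices with respect to adverse health outcomes and health resource consumption". The section on assessing predictive validity answers it with survival models for single or multiple failures, aligned on the first assessment. Its predictor and outcome source are fixed: "FI and CI computed at baseline will be used as predictors of health outcomes documented with the LHC at follow-ups". So is the reading of the result: "These analyses will determine the probability of adverse events over time as a function of the FI, respectively CI, initial scores".

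Data sources and measurement describes both instruments in one sentence. It begins "On each measurement occasion, participants will receive the interRAI-HC, which provides the outcomes used to derive the frailty (FI) and complexity (CI) indices" and goes on to add the LHC, so the LHC is given on all three occasions. On its window the section says that "the tool covers the 6 months preceding each interview", and on its content, "It will assess the history of falls, emergency admissions, hospitalizations and lengths of stays, physician visits and life-striking events". The same section lists the interRAI-HC domains from which index items are drawn. One of them is "falls, physical abilities, physical symptoms and pain (J)".

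Covariates come in by two routes. Under Bias and under Comparing groups, a baseline variable that differs between service groups at p < .05 is carried forward. Under Comparing groups, group itself is a covariate in the survival models for the group-risk question. Neither route names prior events.

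**The concern.** Falls, hospital stays, emergency admissions and physician visits recur. People who had them in the last six months tend to have them again, so the earlier count of the same event is a natural benchmark for any new predictor. The baseline LHC supplies that count, yet the predictive-validity section gives it no role.

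An association between baseline FI and later falls can then arise in two ways. The index may carry new information, or it may partly restate who has recently fallen. The index-only model cannot tell these apart. Overlap is possible because falls are in the interRAI-HC item pool, and the article does not say whether event items are kept out of the indices.

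At stake is what may be claimed afterwards. Research question 4 and the Discussion aim at screening recommendations for homecare nurses. For those, it matters whether a computed index tells a nurse more than the patient's recent history does.

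**Working it through.** **1. The plan's own figure.** Study size gives N = 195 for a within-between interaction with 3 groups, 3 occasions, f(V) = .20, α = .05 and power .90. With s = min(3−1, 3−1) = 2, df1 = 2 × 2 = 4, df2 = 2(N − 3) and λ = N·s·f(V)², N = 195 gives df2 = 384, λ = 195 × 2 × 0.04 = 15.6 and power 0.9001. The figure reproduces. (The other common choice, λ = df2·f(V)², gives 198.) It sizes the Group × Occasion interaction, so it neither supports nor contradicts the present point.

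**2. The passages side by side.**
- Calendar before baseline: collected, six months, same event types.
- Calendar at the two follow-ups: two six-month windows, which make up the 12-month outcome period.
- Model: risk as a function of the initial FI or CI score; no history term and no history-only comparator.
- Covariate screen: selects on difference between service groups, not on prediction of the outcome. A strong predictor that is balanced across groups would stay out.

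**3. Can an index with nothing to add reach p < .05?** The article gives no event rates, heterogeneity or item lists, so the following are assumptions. There are N = 210 participants, 70 per group, with group rate ratios 0.6, 1.0 and 1.4. Each person's rate multiplier u is gamma with mean 1 and variance θ (0.5, 1 or 2), times the group ratio. The prior count is h ~ Poisson(r·u) and the 12-month count y ~ Poisson(2r·u), with r = 0.15 or 0.30 per six months. The index is x = ρ·h* + √(1 − ρ²)·noise, where h* is the standardised prior count capped at 3 and ρ is 0.3, 0.5 or 0.7. Given h, x says nothing about y. The test is a two-sided .05 test from Poisson regression with robust variance, standing in for the multiple-failure model, with 800 replicates per cell.

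| r | θ | ρ | index only | + group | + prior events |
|---|---|---|---|---|---|
| 0.15 | 0.5 | 0.3 | 10.1% | 9.5% | 5.5% |
| 0.15 | 1 | 0.5 | 30.9% | 27.0% | 6.6% |
| 0.30 | 1 | 0.5 | 61.6% | 55.4% | 8.8% |
| 0.30 | 2 | 0.7 | 98.1% | 97.8% | 6.8% |

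Over all 18 cells the ranges are 10.1% to 98.1% (index only), 9.5% to 97.8% (with group) and 5.5% to 9.5% (with prior events). Adjusting for group barely helps; adjusting for history nearly restores the nominal level.

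**4. Dilution across items.** Each index is a sum over many items divided by their number. With one history item among K otherwise uninformative items (600 replicates per cell, same r and θ):
- K = 10: 7.5% to 34.8% index only; 5.7% to 8.7% with history.
- K = 40: 7.0% to 12.7% index only; 4.7% to 7.3% with history.

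The Monte Carlo standard error at 7% is √(0.07 × 0.93/600) ≈ 1 percentage point. The low end for K = 40 therefore cannot be told from the test's own level.

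**5. A second parametrisation.** Assume 0.35 falls per six months, gamma shape 1 and other index variation with SD 0.08 (500 runs). If each prior fall adds 0.02, 0.04 or 0.06 to the index, the rate ratio per 0.1 is 1.11, 1.22 or 1.28, with p < .05 in 14%, 34% or 55% of runs. With prior-event terms added, the ratio is 1.00 and the rate 6% to 9%. With an assumed 40 items, one item can move the index by at most 1/40 = 0.025. The upper two cases need each fall to shift 0.04 × 40 = 1.6 or 0.06 × 40 = 2.4 full items, so only the 14% case resembles a single falls item.

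**The case against.** The strongest reply is that the study asks for predictive validity, not incremental validity. An index-only survival model answers research question 2 as worded, and no section claims that the index outperforms history. That stands: nothing here is a contradiction or a wrong figure.

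A reader might go further and infer that an index which merely restates past events would be declared valid. The document does not support that. It sets no rule for declaring validity, and Statistical methods says the 95% confidence intervals will inform interpretation beyond the p threshold. An index spread over many domains that carries history and nothing else is also a limiting case.

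Nor is the calendar free in practice. It is a separate 15-minute instrument, whereas the index would come from an assessment that nurses already do. An index that fails to beat the calendar need not be useless.

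Over-adjustment is a fair worry too. If falls items belong to the index, conditioning on fall history removes part of the index's own signal. This argues for keeping the index-only model at full standing and for reporting the index with and without such items.

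Two replies carry less weight. The group-difference screen might admit prior events, but it neither names nor guarantees them. A full protocol or analysis plan might cover the matter, but this section already fixes predictor, outcome source, model family and reading. A comparison that uses data in hand is a better analysis to add to it, not a detail that the article omitted.

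**Conclusion.** The point holds in a limited form. The planned models can show that FI or CI predict later events. They cannot show that either adds to the recent event history already recorded at baseline, and an index that partly encodes that history can reach p < .05 for that reason.

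The size is uncertain. It runs from about 7% of runs, close to the nominal level, when history is one item in 40, to nearly all runs when the index tracks history closely. These figures rest on assumed event rates, heterogeneity and index composition, and on Poisson regression in place of the survival models. Age and sex were not simulated. The existence of the gap rests on the text alone.

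**What to change.** Keep the index-only survival models as the answer to research question 2. In the predictive-validity section, add for each recurrent LHC outcome (falls, hospitalizations, emergency admissions, physician visits):
1. a prespecified reference model with age, sex and the baseline-LHC count of the same event;
2. the same model plus FI, respectively CI, reporting the adjusted index coefficient with its 95% confidence interval and the change in concordance.

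Limit any claim of added screening value to this comparison. Where an index contains items for the outcome event, such as interRAI-HC falls items, report it with and without them.

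The cost is one more model per outcome, and the hazard ratios reported for FI and CI will probably be smaller. No new data are needed, and N = 195, raised to 210, is unaffected.

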### Comparing groups with various risks of adverse outcomes

Preliminary analyses will be conducted to assess potential preexisting group differences on baseline sociodemographic and health variables, as the ICHOM recommends [44, 45]. The analyses will be conducted by means of one-way ANOVAs, chi-square tests and Kruskal-Wallis tests, respectively, for continuous, nominal and ordinal dependent variables. Variables demonstrating significant group differences at *p* < .05 will be subsequently used as covariates. Group comparisons on the FI and CI scores will be assessed at baseline using separate linear regressions, with group as predictors (control group as reference) and FI and CI as outcomes. Regression modeling will also be used at the end of data collection to estimate group differences on the evolution of frailty and complexity. The models will include the main effect of group (between subjects) and measurement occasion (within subject), as well as the two-way interaction (Group × Occasion). Finally, to assess group differences in terms of the risk of adverse outcomes, survival analyses will be conducted by including group as a covariate in the analysis design.

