### Participants

The target population is individuals aged 65 or older living in the community, receiving or not, professional home services. Participants will be divided among three samples based on an adverse health outcome risk stratification approach [40]. The criteria used to assign participants to each of the groups sampled is the use of formal home services, viewed as a proxy variable of the degree of vulnerability and risk of adverse outcomes. In the “control” group (lower risk, *N* = 70), participants are free of formal homecare or assistance. In the “assistance” group (medium risk, case 1, *N* = 70), participants are free of formal care but benefit from home assistance at least once a week. The types of services considered as formal assistance are help for household, shopping, meal preparation, transportation, administration and the use of meal delivery services. In the “care” group (higher risk, case 2, N = 70), participants receive formal homecare at least once a week, eventually in addition to formal assistance. Care is a service that the Swiss health insurance system recognizes and that a nurse, a nurse assistant or another health professional provides. Sampling will involve the use of a non-probabilistic convenience method; volunteers meeting the eligibility criteria will be enrolled in the study on a first-come, first-served basis. Eligible participants include men and women aged 65 or older, living in the community. For all participants, the inclusion criteria are as follows: to live in a private dwelling in the canton of Geneva, Switzerland; to be able to hold a meaningful conversation in French; and to be oriented in time and space. The two latter ones are established via the nurses’ clinical judgement at first phone contact, guided by target questions in the eligibility questionnaire. Exclusion criteria are as follows: to live in a long-term facility or in a nursing home; not living in the canton of Geneva, Switzerland; not fluent in French; disoriented in time and space; being subject of trusteeship. Eligibility is determined at first contact (see Fig. 1).

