The EuroQoL EQ-5D-3 L (six items, 5 min [46]) is used to evaluate self-perceived health-related quality of life.

The Mini Nutritional Assessment–Short Form (MNA-SF, seven items, 5 min [47]) is a standardized scale designed to evaluate the nutritional statuses of older adults.

The Montreal Cognitive Assessment (MoCA, 30 items, 20 min [48]) is used to evaluate global cognitive functioning.

Global health status will be assessed by means of an ad hoc questionnaire serving to document self-reported additional health outcomes that include visual and auditory difficulties, frailty status, fear of falling, pain, current pathologies, and alcohol and tobacco consumption. The questionnaire will serve to document the sample characteristics and complements the heath-related data collected with the interRAI-HC with external measures.

Sociodemographic status will be assessed by means of an ad hoc questionnaire that serves to document basic sociodemographic outcomes, including age, sex, educational and professional attainment, living arrangements, living conditions, social participation and caregiving, self-perceived isolation and loneliness, and overall satisfaction with life. The questionnaire will serve to document the sample characteristics and complements the sociodemographic data collected with the interRAI-HC with external measures.

At the end of each assessment, the COMID [37] will be used to assess the multidimensional complexity of the case/situation. It will serve as an external measure of complexity, which serves to assess the convergent validity of the CI derived from the interRAI-HC assessment.

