### Bias

Information bias will be addressed through the double-checking of the criteria used for group assignment, which are first identified based on information collected with the EQ and subsequently adjusted based on data collected at baseline with interRAI-HC. Furthermore, information bias will be addressed via statistically testing group differences on potential confounding variables, such as age, sex, education and living arrangement. Should group differences be significant (*p* < .05) on a given variable, the variable will be used as a covariate in subsequent analyses so as to control for its confounding effect. Selection bias, potentially enhanced by the convenient sampling method, is addressed at recruitment. Calls for participation will be sent out in all municipalities of the canton of Geneva to enhance the representativity of socioeconomic neighborhoods and environments (e.g. urban vs. rural). Furthermore, both public and private home service providers will relay calls for participation among their clients to enhance the representativity of care and service recipients. Interviewer bias, which challenges the quality of the data collected, will be addressed by providing specific training to the nurses in charge of data collection and prior field work. Training will focus on validity (appropriate knowledge of what each instrument actually measures), reliability (appropriate use of homogenous instructions in standardized questionnaires) and quality of data (avoiding missing values). Practice sessions were organized to ensure that the nurses properly master the measurement instruments prior to data collection. Finally, measurement bias will be addressed by using, whenever possible, standardized instruments with documented validity and/or reliability.

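### Covariates for the group comparisons are chosen by a p<.05 baseline screen that includes health variables, which can adjust away part of the baseline FI/CI contrast and can drop real confounders

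*Protocol article*

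**What the plan says.** All references are to the Protocol article.

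- **Comparing groups with various risks of adverse outcomes.** "Preliminary analyses will be conducted to assess potential preexisting group differences on baseline sociodemographic and health variables". The tests are "one-way ANOVAs, chi-square tests and Kruskal-Wallis tests, respectively, for continuous, nominal and ordinal dependent variables". Variables significant at p<.05 "will be subsequently used as covariates". The section then regresses FI and CI on group at baseline (control as reference), models group, occasion and their interaction over follow-up, and includes group in survival analyses.
- **Bias.** The same p<.05 rule applies to "potential confounding variables, such as age, sex, education and living arrangement". If groups differ, "the variable will be used as a covariate in subsequent analyses so as to control for its confounding effect".
- **Participants.** Groups are defined by use of formal home services, "viewed as a proxy variable of the degree of vulnerability and risk of adverse outcomes".
- **Data sources and measurement.** Besides the interRAI-HC, the baseline visit includes the EQ-5D, MNA-SF, MoCA and a health questionnaire covering "visual and auditory difficulties, frailty status, fear of falling, pain, current pathologies, and alcohol and tobacco consumption".
- **Primary outcome measures.** FI and CI are each a sum of interRAI-HC items divided by the number of items.

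No covariate is fixed in advance, and no health variable is excluded from the screen.

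**The concern.** A group-difference test is a poor way to choose covariates here, for two separate reasons.

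**Over-adjustment.** The three groups are meant to differ in vulnerability. Nutrition, cognition, quality of life and self-reported health, including a self-reported frailty status, should therefore differ between them and tend to pass the screen. These are other readings of what FI and CI are meant to capture. Once they enter the model, the group coefficient answers a different question: how FI differs between groups among people who are already equally ill, malnourished or cognitively impaired.

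**Dropped confounders.** Whether a variable passes depends on the sample size and the observed group difference, not on its relation to FI or CI. Age or education may differ enough to distort the contrast and still miss p<.05.

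At stake are the baseline FI/CI group regressions, the group main effect in the longitudinal model, and any covariate-adjusted group comparison in the survival analyses.

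**Working it through.** **1. The plan's own figures.** Study size gives N = 195 for the within-between interaction (3 groups, 3 occasions, f(V) = .20, α = .05, power .90). With s = 2, df1 = 4, df2 = 2 × (195 − 3 − 2 + 2) = 384 and λ = 2 × 195 × 0.20² = 15.6, the noncentral F gives power 0.900, so the figure reproduces. The planned baseline size is 325 × 0.30 × 0.90, about 87 per group. The baseline contrast should be judged at 87 per group; 70 is the size at 12 months.

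**2. What the rule cannot move.** In the Group × Occasion model, a baseline covariate entered as a main effect is constant within a person. It cancels from every within-person difference between occasions. With complete data the four interaction coefficients are therefore the same with and without it; a numerical check confirmed this. Observed rates and the construction of the indices involve no covariates.

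**3. Over-adjustment at baseline.** These inputs are assumptions, because the article gives none:
- a vulnerability factor with group means 0, 0.4 and 0.8 SD;
- FI loading .9 on that factor, so the true care-versus-control contrast is 0.9 × 0.8 = 0.72 SD;
- three health scales, each with loading r;
- 87 per group.

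If all three scales are kept, the fraction of the contrast that survives is 1 / [1 + 3r²/(1 − r²)]. At r = .5 this is 1/(1 + 3 × 0.25/0.75) = 0.50. Simulating the p<.05 screen itself gives less shrinkage at low loadings, because not every scale passes.

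| Loading r | Shrinkage if all three kept | Shrinkage with the screen (simulated) | Contrast left (of 0.72 SD) | Power (unadjusted: over 99%) |
|---|---|---|---|---|
| .3 | 23% | about 12% | 0.63 | about 99% |
| .4 | 36% | about 25% | 0.54 | about 97% |
| .5 | 50% | about 43% | 0.41 | about 88% |
| .6 | 63% | about 60% | 0.29 | about 67% (up to 71% in repeat runs) |
| .7 | 74% | about 74% | 0.19 | about 44% |

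With 70 per group, one to six scales, loadings .3 to .7 and a factor difference of 0.8 to 1.2 SD, simulated shrinkage runs from 4% to about 86%.

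**4. Dropped confounders.** Take a continuous confounder with group means 0, d/2 and d (in SD). Then λ = n × d²/2 with 2 and 3n − 3 degrees of freedom. For n = 87 and d = 0.3, λ = 87 × 0.09/2 = 3.9.

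| d (control to care) | Passes screen, n = 87 | Passes screen, n = 70 |
|---|---|---|
| 0.2 | 20% | 17% |
| 0.3 | 40% | 33% |
| 0.4 | 65% | 55% |
| 0.5 | 84% | 75% |

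In simulations with 70 per group, no true group effect, d = 0.2 to 0.4 and a confounder-outcome slope of 0.3 to 0.5, the bias in runs where the confounder was dropped was 0.05 to 0.13 SD. Adjusting for it in every run left the estimate within 0.01 SD of zero.

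**The case against.** **Much of the study is untouched.** This stands. The sample size rests on the interaction, which step 2 shows is unmoved with complete data. Research question 3 asks about rates and their change, and observed rates need no covariates. A reader might infer that every group result is compromised; the documents do not support that.

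**The direction is not fixed.** This also stands. It is tempting to say that the contrast must be biased toward no difference. Over-adjustment does that, but a dropped confounder can push the other way, for example if the care group is older. The dropped-confounder part is also modest beside an assumed 0.72 SD contrast, and larger imbalances usually pass the screen.

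**Overlap of content is not proved item by item.** The article does not list the FI or CI items, and both come from the interRAI-HC alone. The MNA-SF, MoCA and EQ-5D are separate instruments, used to describe the sample. Identity of content is therefore not shown. Overlap in construct is: the interRAI-HC domains include cognition, nutrition, diagnoses, falls and pain, and the health questionnaire records frailty status.

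**The two sections can be read together.** The list under Bias is introduced as examples, so it does not contradict the wider screen. An analysis plan not shown might narrow the set, and nothing forbids unadjusted results. But the rule as published names health variables and says that those passing will be covariates. That is a stated rule, not a detail left open.

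**Conclusion.** The point holds for the baseline FI/CI group regressions, the group main effect in the longitudinal model and any covariate-adjusted group survival comparison. Followed as written, the rule is expected to adjust FI and CI for measures of the same construct, and it leaves the control of real confounders to a significance test.

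The size depends on correlations that the article does not give. Under the assumptions shown, the loss is slight if the health scales relate weakly to frailty (about 12% at loading .3), and it exceeds half of the contrast from loading .6 upward. The existence of the rule is certain; the size of the harm is not. Neither N = 195 nor N = 210 changes. This should be fixed, but it does not undermine the study's main purpose of deriving the indices.

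**What to change.** Under Bias and under Comparing groups with various risks of adverse outcomes:

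1. Replace the p<.05 rule with a fixed covariate set for all group comparisons: age, sex, education and living arrangement, which the Bias section already names.
2. State that FI/CI group models are not adjusted for health measures that reflect frailty or complexity (MNA-SF, MoCA, EQ-5D, the health questionnaire).
3. Report unadjusted group contrasts alongside the adjusted ones.
4. Keep the baseline tests as description only.

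Statistical methods allows a stricter threshold when covariates are required. With a fixed covariate set that condition is always met, so the significance level should be stated outright.

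The cost is wording and a few degrees of freedom at the planned sample size. No new data are needed.
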